#### Recruitment and randomization of GP practices

We will recruit 30 general practices, representing approximately 5% of the total number of practices from the target areas in the northwest of England. All general practices that fall within the catchment area of the trial will be eligible for inclusion. Practices will be allocated to collaborative care or usual care using a central randomization service provided by the Clinical Trials Unit at the Christie NHS Foundation Trust, Manchester, UK. Randomization will be by minimization based on practice size and area deprivation using the Index of Multiple Deprivation [45]. In addition, we will target areas of the northwest (for example, East Lancashire) that have a high density of people from BME groups, especially South Asians. This policy will allow us to enroll sufficient numbers of patients of South Asian origin to pilot-test the acceptability of the intervention in this group. In this trial, participants of South Asian origin are defined as people born in India, Pakistan, Bangladesh and Sri Lanka and their descendants, but excluding those born (or descended from those born) in Nepal, Bhutan, the Maldives, Tibet, Afghanistan, or the Islamic Republic of Iran [46].

Recruitment and training will be undertaken in two sequential waves. This strategy will allow more flexibility when recruiting IAPT and general practices and offers opportunities to: 1) stagger recruitment of IAPT teams and general practices, and 2) run two separate rounds of case-finding, thereby concentrating data collection around fixed periods in the trial calendar, leading to more feasible project management.

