### Patient recruitment

#### Sample size

Based on a UK trial of collaborative care for major depressive disorder [29] we have powered this trial to detect a standardized effect size of 0.4. If each of the 30 practices (15 in each arm) recruits 15 patients at baseline (450 in total), the study will have > 80% (81.2%) power to detect this size of effect at the 5% level of significance, allowing for an intraclass correlation coefficient (ICC) of 0.06 (that was identified in a previous Phase II trial of collaborative care) and a 20% attrition rate.

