### Analysis

The method of allocation of practices to the collaborative care or control arm will be based on simple randomization (that is, 50:50 chance) for the first six practices. Minimization will be used thereafter with 0.7/0.3 probabilities. For each allocation, the balance score will be estimated based on thresholds for practice list size and deprivation, measured using the Index of Multiple Deprivation.

All analyses will be conducted on an intention-to-treat basis subject to the availability of data. After data cleaning, the preliminary analysis will investigate the pattern of missing baseline and follow-up data. The effect of the collaborative-care treatment program on depression outcomes will be estimated using a multi-level mixed-effects linear regression model, including a random effect for practices, and controlling for the following baseline covariates: patient age, gender, ethnicity, and baseline PHQ-9 score. Given that the continuous outcomes are likely to have a skewed distribution, bootstrap sampling (a method free from parametric assumptions) will be used to derive estimates of error variance for the tests of statistical significance, using 10,000 samples. Sensitivity analysis will be carried out to check the implications of different assumptions about the missing data.

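### Practices are minimised on list size and deprivation, but the outcome model omits both; if they are prognostic, the test is somewhat conservative and some power is forgone

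*Protocol article*

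**What the plan says.** On allocation, the section on recruitment and randomization of GP practices states: "Randomization will be by minimization based on practice size and area deprivation using the Index of Multiple Deprivation". The Analysis section adds the mechanics: "simple randomization (that is, 50:50 chance) for the first six practices", then "Minimization will be used thereafter with 0.7/0.3 probabilities", where "the balance score will be estimated based on thresholds for practice list size and deprivation".

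On analysis, the same section specifies a multilevel linear model for the depression outcomes, "including a random effect for practices, and controlling for the following baseline covariates: patient age, gender, ethnicity, and baseline PHQ-9 score". Neither list size nor deprivation is in that list. For the tests, bootstrap sampling "will be used to derive estimates of error variance for the tests of statistical significance, using 10,000 samples". The unit to be resampled is not stated.

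On power, the Sample size section says "we have powered this trial to detect a standardized effect size of 0.4" and gives 81.2% power at the 5% level with 30 practices of 15 patients, an ICC of 0.06 and 20% attrition.

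The economic ANCOVA (Health economics analysis, Costs) is described as adjusting for baseline differences at practice level as well as patient level. The clinical model has no practice-level covariate. The article gives no reason for choosing the two minimisation factors and no figure for how strongly they predict depression outcome.

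**The concern.** Minimisation pushes the two arms towards balance on its factors. If a balanced factor is prognostic and left out of the model, its contribution stays in the estimated between-practice variance, although much of it has been removed from the comparison of arms. The model-based standard error then exceeds the true sampling variability of the estimate. The test rejects less often than its nominal 5%, and part of the precision that minimisation could have bought is not used.

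This matters more than usual here because practices are few and the between-practice component is large. With an ICC of 0.06 and 12 patients analysed per practice, it makes up 0.06 / (0.06 + 0.94/12) = 0.06 / 0.1383, or about 43%, of the variance of a practice mean.

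**Working it through.** **Inputs from the protocol article.** Effect 0.4 SD; 15 practices per arm; 15 patients per practice, less 20% attrition, so 12 analysed; ICC 0.06; 5% level, taken as two-sided because sidedness is not stated; first six practices by simple randomization, then minimisation with probabilities 0.7/0.3.

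**Assumption.** R is the share of between-practice variance, remaining after the listed patient covariates, that the two factors explain. The documents give no value, so a range is shown.

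**The plan's own figure.** Design effect = 1 + (12 − 1) × 0.06 = 1.66. Effective number per arm = 180 / 1.66 = 108.4. SE = √(2 / 108.4) = 0.1358 SD. A noncentral t with 28 degrees of freedom gives power of 81.1%, which reproduces the stated 81.2%.

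**Formula with both factors in the model.** SE = √(2 × [0.06(1 − R) + 0.94/12] / 15), with 26 degrees of freedom.

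- R = 0: SE 0.136, power 80.9%
- R = 0.1: SE 0.133, power 82.6%
- R = 0.3: SE 0.127, power 86.0%
- R = 0.5: SE 0.120, power 89.3%
- R = 0.8: SE 0.110, power 93.9%

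**Simulation of the stated allocation.** Two independent binary factors of equal prevalence and equal weight; 30 practices; analysis of practice means by t test with and without the factors; 8,000 trials per scenario. The Monte Carlo standard error is √(0.05 × 0.95 / 8000), about 0.24 points, on type I error and √(0.8 × 0.2 / 8000), about 0.45 points, on power.

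| R | Unadjusted: mean model SE / true SE | Ratio | Type I error, unadjusted | Power, unadjusted | Power, adjusted |
|---|---|---|---|---|---|
| 0 | 0.1361 / 0.1373 | 0.99 | 5.5% | 80.3% | 79.1% |
| 0.1 | 0.1360 / 0.1348 | 1.01 | 5.0% | 81.6% | 81.6% |
| 0.3 | 0.1369 / 0.1307 | 1.05 | 4.0% | 81.8% | 84.7% |
| 0.5 | 0.1368 / 0.1277 | 1.07 | 3.9% | 82.5% | 88.1% |
| 0.8 | 0.1370 / 0.1213 | 1.13 | 2.8% | 83.4% | 93.3% |

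A separate run of 6,000 trials per scenario agrees. At R = 0.3 it gave type I error of 3.6% and power of 81.9% unadjusted against 85.3% adjusted. At R = 0.5 it gave 3.4%, and 82.9% against 88.8%. At R = 0 adjusting cost about 1.5 points.

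**With a bootstrap that resamples practices.** Unadjusted difference in means; 4,000 trials per scenario; 300 resamples each; cut-off 1.96.

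| R | Mean bootstrap SE / true SE | Ratio | Type I error |
|---|---|---|---|
| 0 | 0.1339 / 0.1355 | 0.99 | 6.3% |
| 0.1 | 0.1341 / 0.1337 | 1.00 | 5.8% |
| 0.3 | 0.1340 / 0.1315 | 1.02 | 5.5% |
| 0.5 | 0.1341 / 0.1275 | 1.05 | 5.1% |
| 0.8 | 0.1345 / 0.1205 | 1.12 | 3.8% |

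At R = 0 this version rejects slightly too often, so its type I error near 5% at R = 0.3 to 0.5 is partly two errors cancelling. An adjusted bootstrap was not simulated, so no like-for-like power loss is given for it. If patients were resampled instead, the SE would be about √(2/180) = 0.105, which is too small.

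**The case against.** The strongest reply is that the harm depends on a quantity the documents do not supply. If the factors explain 10% or less of the residual between-practice variance, omitting them costs nothing, and if they explain none, adjusting costs a point or so. Area deprivation may also act partly through ethnicity and baseline PHQ-9, which are already in the model, so the relevant share could be small. This stands, and it is why the point has to be conditional. The Process evaluation section does list socioeconomic status among possible predictors of improvement, next to age, gender and ethnicity, which are in the model. That makes relevance plausible but does not measure it.

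A second reply is that the t tests simulated above are not the planned test, which takes its error variance from a bootstrap. This also stands in part. Resampling practices makes the overstatement smaller but does not remove it at R = 0.5, and because the resampling unit is unstated it cannot be counted on as the remedy.

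A third reply is that six simple allocations followed by a 0.7/0.3 rule give only loose balance, which weakens the effect. That loose balance is already in the simulation. It also leaves chance imbalance that adjustment would remove: at R = 0.5 the true SE is 0.128 unadjusted and 0.123 adjusted.

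Finally, a full analysis plan might add the factors. The article, however, states a closed covariate list, so this is a stated choice and not a matter left open.

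**Conclusion.** The mismatch between allocation and analysis is real and is in the text. Its consequence is conditional and moderate. If the two factors explain 30 to 50% of residual between-practice variance, the model-based standard error is about 5 to 7% too large, type I error is about 3.4 to 4.0%, and about 3 to 6 points of power are forgone. The loss reaches about 10 points only at an extreme 80%. These figures rest on binary factors, equal practice sizes, analysis of practice means without patient covariates, and an assumed R.

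Stronger readings are tempting but not supported:

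- A reader might infer that the standard error is certainly overstated. That needs R, which is not given, and it also depends on the bootstrap's resampling unit.
- A reader might infer that the 81.2% power claim is wrong. It is reproduced, and the simulated t tests without the factors keep power at about 80 to 83% at every R examined. The loss is only relative to a better model.
- A reader might infer that all the benefit of minimisation is lost. The true unadjusted SE still falls, from 0.137 at R = 0 to 0.128 at R = 0.5.
- A reader might infer bias. Omitting the factors does not bias the treatment estimate.

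The trade still favours adjusting: a cost of about 1 to 1.5 points if the factors are irrelevant, against 3 to 6 points gained if they matter moderately. It should be changed, but it does not threaten the validity of the trial.

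**What to change.** In the Analysis section, add practice list size and Index of Multiple Deprivation, in the thresholded form used for minimisation, as fixed practice-level covariates in the primary mixed model. If the investigators prefer to leave them out, they should give the reason before any unblinded analysis.

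The cost is one sentence and two practice-level degrees of freedom (26 instead of 28). No new data are needed, because allocation already requires both values. The economic ANCOVA already provides for practice-level adjustment, so it needs no change beyond using the same two factors.

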**Methods:**

This is a cluster randomized controlled trial of 30 general practices allocated to either collaborative care or usual care. Fifteen patients per practice will be recruited after a screening exercise to detect patients with recognized depression (≥10 on the nine-symptom Patient Health Questionnaire; PHQ-9). Patients in the collaborative-care arm with recognized depression will be offered a choice of evidence-based low-intensity psychological treatments based on cognitive and behavioral approaches. Patients will be case managed by psychological well-being practitioners employed by IAPT in partnership with a practice nurse and/or general practitioner. The primary outcome will be change in depressive symptoms at 6 months on the 90-item Symptoms Checklist (SCL-90). Secondary outcomes include change in health status, self-care behaviors, and self-efficacy. A qualitative process evaluation will be undertaken with patients and health practitioners to gauge the extent to which the collaborative-care model is implemented, and to explore sustainability beyond the clinical trial.

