Remission is common for mild to moderate depression, and the ability of this trial to detect treatment effects will be improved if the sample includes only patients with persistent depressive symptoms. To exclude patients with transient and spontaneously remitting depression research staff blinded to the intervention allocation will therefore visit patients who scored greater than or equal to 10 on the initial telephone PHQ-9 screen to undertake a second PHQ-9 screen. Patients who score greater than or equal to 10 at this second PHQ screening appointment will then be invited to complete baseline assessments and enter the trial. The researcher will tell the participant’s GP about their involvement in the study. Patients who score less than or equal to 9 at this second screening appointment will be informed that they do not meet the study inclusion criteria and will be excluded; their GP will be informed by the research team that they will take no further part in the study at this stage. A CONSORT flow diagram of the recruitment and screening strategy is shown in Figure 1.

Researchers blinded to the intervention allocation will forward the details of those patients who are eligible to join the trial (those who scored ≥10 on PHQ-9 at the second screening appointment) to the COINCIDE trial manager. The trial manager will enter these details onto a password-protected and encrypted database. Within 3 working days of the second screening appointment, the trial manager will contact the clinical lead of the IAPT team to pass on contact details of patients in the collaborative-care arm who have met the inclusion criteria. PWPs will then contact the patient directly to set up a first appointment.

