### Outcome assessment

#### Primary outcome

The mental-health needs of people with LTCs have historically been under-recognized and under-served in primary care, and the main aim of this trial is to improve the access to and quality of depression care for people with two exemplar LTCs: diabetes and/or CHD. The interventions used are designed primarily to improve depression rather than both depression and physical health outcomes. The primary outcome in this trial is therefore change in depressive symptoms. However, using low-intensity psychological interventions, including lifestyle counseling, to treat depression may also be beneficial for diabetes/CHD, leading to opportunities for therapeutic synergies across multiple conditions. Accordingly, we will also test the effects of collaborative-care interventions on a range of secondary outcomes related to diabetes and CHD and self-care.

The 90-item Symptoms Checklist (SCL-90) depression scale will be used to assess changes in severity of depressive symptoms at 6-months [64]. Response to treatment is defined as greater than or equal to 40% reduction in SCL-90 scores [65]. We will also use the PHQ-9 at baseline and follow-up to measure changes in dichotomous diagnosis of depression [48].

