### Measure of contamination

It is possible that PWPs trained by CLAHRC might share knowledge and training about collaborative care with colleagues not enrolled in the COINCIDE trial, thereby subverting the study protocol and threatening the internal validity of the study. However, non-CLAHRC trained PWPs will not be using collaborative care for the duration of the trial when they encounter patients with depression and diabetes/CHD. Thus, the effects of contamination caused by knowledge sharing between PWPs are likely to be minimal. We will measure the effect of contamination between CLAHRC-trained and non-CLAHRC-trained PWPs by assessing changes in knowledge, attitudes, and clinical practice between baseline and follow-up, using previously validated approaches to evaluate depression training programs [88].

The schedule of assessments is shown in Table 2.

**Table 2 T2:** Schedule of assessments

**Patient assessments**	**Time point**		
	**Screening**	**Baseline**	**6 months**
PHQ-9	X	X	X
Demographic variables, past medical and psychiatric history		X	
Current physical illness details (including medication)		X	
Number and burden of diseases		X	
RSQ		X	
Self-efficacy measure		X	X
SCL-90 depression		X	X
EQ-5D		X	X
GAD-7		X	X
DQoL		X	X
SAQ		X	X
WHOQoL-BREF		X	X
heiQ		X	X
ESSI		X	X
AIPQ		X	X
SDS		X	X
Anti-depressant prescription rate and referral to other MHS			X
Healthcare utilization (purpose-designed questionnaire)			X
PACIC			X
CSQ			X
Practitioner assessment			
Change in KAP		X	X

Abbreviations: AIPQ, Adapted Illness Perceptions Questionnaire; CSQ, Client Satisfaction Questionnaire; DQoL, Diabetes Quality of Life; ESSI, Enhancing Recovery in Coronary Heart Disease (ENRICHD) Social Support Instrument; EQ-5D, the five-domain EuroQoL quality of life questionnaire; GAD-7, the seven-item Generalized Anxiety Disorder questionnaire; heiQ, Health Education Impact Questionnaire; KAP, Change in Knowledge, Attitudes, Practice; MHS, mental-health service; PACIC, Patient Assessment of Chronic Illness Care; PHQ-9, the nine-item Patient Health Questionnaire; RSQ, Relationship Scales Questionnaire; SAQ, Seattle Angina Questionnaire; SCL-90, the 90-item Symptoms Checklist; SDS, The Sheehan Disability Scale; WHOQoL-BREF, World Health Organization Quality of Life brief measure.

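### The primary model adjusts for baseline PHQ-9 but not for baseline SCL-90 depression, which is collected, so available precision is given up

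*Protocol article*

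**What the plan says.** The Primary outcome section of the protocol article states: "The 90-item Symptoms Checklist (SCL-90) depression scale will be used to assess changes in severity of depressive symptoms at 6-months". The Abstract also defines the primary outcome as change on this scale at 6 months. Table 2 has a row for "SCL-90 depression" marked at both baseline and 6 months, so every participant should have a baseline value.

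The Analysis section states: "The effect of the collaborative-care treatment program on depression outcomes will be estimated using a multi-level mixed-effects linear regression model". It includes a random effect for practices, "controlling for the following baseline covariates: patient age, gender, ethnicity, and baseline PHQ-9 score". Baseline SCL-90 is not in that list and no other section adds it. The article also does not say whether the dependent variable is the 6-month score or the change from baseline.

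PHQ-9 has two other roles. It is the entry criterion: "Patients who score greater than or equal to 10 at this second PHQ screening appointment will then be invited to complete baseline assessments". At follow-up it serves a separate purpose: "We will also use the PHQ-9 at baseline and follow-up to measure changes in dichotomous diagnosis of depression".

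**The concern.** The baseline value of an outcome is usually its best single predictor. Here it is collected but left out of a covariate list that the article states explicitly, so this is a stated choice and not a detail left to an unseen analysis plan. PHQ-9 is a related but different instrument. The entry rule of 10 or more on two occasions cuts its range, which tends to weaken it as a stand-in.

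Both readings of the dependent variable are affected. With the 6-month score, a strong predictor is missing. With the change score, baseline SCL-90 enters only by subtraction, with a coefficient fixed at one, which over-corrects when the true coefficient is below one.

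At stake is the width of the primary confidence interval, and how far the estimate follows whatever SCL-90 difference happens to exist between arms at baseline. Only 30 practices are randomized, and minimization uses practice size and deprivation, not depression. The economic analysis already follows the principle: prior costs are a covariate for later costs.

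**Working it through.** **Inputs from the protocol article (Sample size section).** Effect 0.4 SD; 15 practices per arm; 15 patients per practice, so 225 per arm; 20% attrition, leaving 12 per practice; ICC 0.06; 5% level (two-sided assumed); stated power 81.2%.

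**Assumed inputs, not in the documents.** Let *a* be the correlation of 6-month with baseline SCL-90, *b* that of 6-month SCL-90 with baseline PHQ-9, and *c* that between the two baselines. The main illustration uses *a* = 0.5, *b* = 0.3, *c* = 0.5. SCL-90 SDs are taken as equal at both times and set to 1. The ICC of baseline SCL-90 is taken as 0.06.

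**Step 1: reproduce the stated power.** Var(effect) = (2/15) × (0.06 + 0.94/12) = 0.01844, so SE = 0.136. With a t distribution on 30 − 2 = 28 df, power is 81.1%, matching 81.2%. No covariate enters this figure.

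**Step 2: residual variance at 0.5/0.3/0.5.**
- 6-month score given PHQ-9: 1 − b² = 0.91.
- Change score given PHQ-9: 2 − 2a − (b − c)² = 1 − 0.04 = 0.96.
- With baseline SCL-90 added: R² = (a² + b² − 2abc)/(1 − c²) = 0.19/0.75 = 0.253, leaving 0.747. This holds for either dependent variable.
- Reduction: 1 − 0.747/0.91 = 18%, or 1 − 0.747/0.96 = 22%.

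**Step 3: power for 0.4 SD, 6-month score.**
- Reduction at both patient and practice level: SE 0.130 to 0.117, power 84.6% to 90.8%.
- Reduction at patient level only: SE 0.132 to 0.126, power 83.1% to 86.7%.

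For a change score adjusted for PHQ-9 only, the starting power is 82.7% or 82.0% respectively.

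**Step 4: other assumed correlations, 6-month score.** These are illustrations, not bounds.

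| a / b / c | PHQ-9 only | Plus SCL-90 | Reduction | Power, both levels | Power, patient level only |
|---|---|---|---|---|---|
| 0.4 / 0.5 / 0.7 | 0.750 | 0.745 | 1% | 90.7% to 90.9% | 86.6% to 86.7% |
| 0.5 / 0.5 / 0.7 | 0.750 | 0.706 | 6% | 90.7% to 92.3% | 86.6% to 87.6% |
| 0.6 / 0.4 / 0.6 | 0.840 | 0.638 | 24% | 87.3% to 94.5% | 84.6% to 89.0% |
| 0.7 / 0.5 / 0.7 | 0.750 | 0.510 | 32% | 90.7% to 97.8% | 86.6% to 91.7% |

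**Step 5: what a chance imbalance does to the estimate (0.5/0.3/0.5).**
- SD of the arm difference in baseline SCL-90: √[2 × (1 + 14 × 0.06)/225] = 0.128.
- Part left after PHQ-9 adjustment: 0.128 × √(1 − 0.25) = 0.111.
- Coefficient of baseline SCL-90 given PHQ-9: (a − bc)/(1 − c²) = 0.35/0.75 = 0.467. For a change score it is 0.467 − 1 = −0.533.
- Typical shift: 0.111 × 0.467 = 0.052 SD, or 0.111 × 0.533 = 0.059 SD in the opposite direction. Against 0.4 these are 13% and 15%.

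**Step 6: one loss, not two.** The variance carried by the omitted baseline is 0.467² × 0.75 = 0.163, exactly the fall in Step 2 (0.91 − 0.747). For the change score, 0.533² × 0.75 = 0.213 = 0.96 − 0.747. The imbalance is the precision loss seen in a single realization.

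**The case against.** The strongest reply is that nothing here is invalid. Randomization makes the contrast unbiased on average, type I error is not inflated, and the 81.2% power holds without any covariate. At the main illustrative values the plan as written keeps 82% or more. Baseline severity is not ignored either, since PHQ-9 absorbs part of both variance and imbalance. The size of the gain rests wholly on correlations the documents do not give, and at some plausible values it nearly vanishes. All of this stands, and it makes the point a recommended improvement and not a necessary correction.

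A reader might infer more, and four such inferences fail:
- **That 0.128 SD of baseline imbalance is about a third of the target effect.** A baseline difference reaches the estimate only after PHQ-9 adjustment and multiplication by the partial coefficient, which leaves 0.05–0.06 SD, well below the SE of about 0.13.
- **That a change score leaves regression to the mean as a bias between arms.** It is equal in both arms in expectation; the cost is again precision.
- **That imbalance is likely to be systematic because practices may be allocated before patients enter.** The article describes case-finding by mailing and screening by blinded researchers. It does not show selective recruitment.
- **That every continuous outcome should have its own baseline added.** The covariate list is stated for depression outcomes. The models for the other scales are not specified here and may properly sit in the analysis plan.

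**Conclusion.** The point holds as one of efficiency. The stated model leaves out the baseline value of the primary scale, although the trial collects it, and PHQ-9 replaces it only in part. At 0.5/0.3/0.5 the loss is about 18% of residual variance for the 6-month score, or 22% for a change score; for the 6-month score that is power of 83–85% where 87–91% was available. Over the other combinations worked through for the 6-month score, the reduction runs from about 1% to 32%.

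That the covariate is omitted is certain from the text. How much it costs is not, because it depends on the three assumed correlations, on equal SDs, and on how far the covariates explain variation between practices. The documents do not support calling the primary estimate biased or the sample size inadequate.

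**What to change.** In the Analysis section, name the 6-month SCL-90 depression score as the dependent variable of the primary model and add baseline SCL-90 depression score to the covariates. Keep baseline PHQ-9, age, gender, ethnicity and the practice random effect. With baseline SCL-90 in the model, a 6-month score and a change score give the same treatment effect, so this also settles what is meant by change.

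The cost is one line of wording, with no new data and no further patients. The change should be recorded before outcomes are compared by arm (data analysis is forecast to start in August 2013), because adding the covariate after an imbalance has been seen would look data-driven.
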